# **10 CONCOMITANT MEDICATIONS AND TREATMENTS**

## **10.1 Rescue Medication for BV**

Currently, antibiotics represent the treatment of choice for BV and these may be administered either orally or topically as detailed below:

Oral: Metronidazole 500 mg twice daily for 7 days;

Topical: Clindamycin 2% cream, 5 g daily for 7 days.

At any time during the study where a subject presents with a Nugent Score of 7 – 10, the subject will be treated for BV as deemed appropriate by the treating physician. Subjects requiring antibiotic treatment will be discontinued from the study.

## **10.2 Permitted Medications and Treatments**

Any medication and/or treatments in use at the time of the Day 1 visit for any inter-current illness should remain constant for the duration of the study, as evaluated by the Investigator.

## **10.3 Medications and Products not Permitted During the Study**

Any form of antibiotic is forbidden during the course of this study. The subject will be discontinued from the study if antibiotic is given to treat any medical conditions. In the event of a Nugent Score greater than or equal to seven (7), the subject will be discontinued from the study and prescribed an antibiotic as evaluated by the Investigator. Vaginal lubricants and any product applied vaginally are not permitted during the study.

# **11 SAFETY REPORTING**

Adverse Events are defined using the ICH Clinical Safety Data Management (ICH E2A) definition.

## **11.1 Adverse Event**

An adverse event is any untoward medical occurrence in a subject administered an INHP at any dose, which does not necessarily have a causal relationship with this treatment. An adverse event can therefore be any unfavourable and unintended sign, symptom, or disease temporally associated with the use of an INHP, whether or not related to the INHP.

For all adverse events, an assessment must be made of the seriousness, intensity and relationship to the administration of the INHP.

## **11.2 Serious Adverse Event**

A serious adverse event (SAE) is defined as any untoward medical occurrence that at any dose:

- Results in death;
- Is life-threatening;
- Requires inpatient hospitalization or prolongation of existing hospitalization;
- Results in persistent or significant disability/incapacity; or
- Is a congenital anomaly/birth defect.

Medical and scientific judgement should be exercised in deciding whether expedited reporting is appropriate in other situations, such as important medical events that may not be immediately life-threatening or result in death or hospitalization but may jeopardize the subject or may require intervention to prevent one of the outcomes listed in the definition above. These should also usually be considered serious.

A life-threatening event is any event in which the subject was at risk of death at the time of the event; it does not refer to an event, which hypothetically might have caused death if it were more severe.

A serious unexpected adverse reaction is any serious adverse reaction that is not identified in nature, severity or frequency in the risk information set out on the label of the natural health product.

### 11.3 Reporting of Serious Adverse Events

All serious adverse events fulfilling the definition of seriousness and occurring during the clinical study (i.e. following informed consent and up to the end of the additional follow-up period) must be reported immediately (*within 24 hours of the Investigator's awareness*) to Integrated Research Inc. Serious Adverse Events occurring before the INHP or placebo is taken will not be captured.

In case of a serious adverse event, please complete the Serious Adverse Event (SAE) Form provided for the study and fax it immediately to:

Attn: [name]  
Integrated Research Inc.  
[contact]

The Investigator must complete the SAE Form by providing at least: protocol identification, subject's initials and number, date of birth, period of the INHP use, nature of the adverse event and the relationship to the INHP.

The cause of death of a subject in a study should be reported as a serious adverse event. Death should not be reported as an adverse event, but as an outcome. The only exception is *sudden death* (when the cause of death is unknown), which is reported as a serious adverse event with death as the outcome.

In case of pregnancy during the clinical study, the subject should be discontinued from the study and the event reported. The outcome of the pregnancy should also be reported.

*Unexpected adverse event* is an adverse event of which the nature or severity is not consistent with the applicable product information.

In accordance with the ICH GCP Guidelines and Natural Health Products Regulations, the Sponsor will report all serious adverse NHP reactions to the Natural Health Product Directorate (NHPD) and local Ethics Committee.

## 12 SUBJECT WITHDRAWAL

Subjects have the right to withdraw from the study at any time and for any reason. In the event that a subject withdraws, every effort must be made to obtain "End-of-Treatment" information by completing, within the shortest delay, the assessments and procedures planned at Visit 8 – Day 47. The reason(s) for withdrawal must be described, and if more than one is given, the Investigator must specify the primary reason.

The Investigator will maintain the subject in the study as long as possible. However, the Investigator may also decide to withdraw a subject from the study in any of the following circumstances apply:

- Subject no longer meets the inclusion or exclusion criteria;
- Nugent Score less than three (3) or greater than six (6);
- Occurrence of an adverse event for which, in the opinion of the Investigator, the continuation of the study may compromise the safety of the subject; and
- Pregnancy.

In the case of withdrawal due to an adverse event which may potentially be related to the investigational products, the subject should be followed up until all abnormalities return to acceptable levels or stabilize. All adverse events must be documented on the corresponding pages in the case report form.

Any premature termination of treatment must be reported immediately to the Sponsor's designated representative.

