#### **5.1.3 Diagnosis**

Clinicians consider the Nugent scoring system, first described in 1991, as the gold standard for diagnosing BV. Nugent diagnosis relies on the detection of vaginal epithelial cells infected by coccobacilli, the so-called "clue cells", upon microscopic examination of a Gram-stained smear of vaginal discharge.

The Nugent Score is calculated by assessing for the presence of:

- Large gram-positive rods (lactobacilli; Scored as 0 to 4);
- Small gram-variable rods (Scored as 0 to 4); and
- Curved gram-variable rods (Scored as 0 to 2).

The Nugent Score can range from 0 to 10 with a Score of >7 consistent with BV and a Score from 4 to 6 indicative of an intermediate microbiota. A Nugent Score from 0 to 3 indicates a normal status. Women with an intermediate Score have an approximately equal probability of developing either BV or a normal microbiota.

Using the “Amsel” set of clinical criteria in combination with the Nugent scoring system provides a simple and reliable tool for confirming BV presence. According to Amsel criteria BV may be defined by the following clinical signs:

- Vaginal pH >4.5;
- Presence of adherent white discharge;
- Detection of “clue cells”; and
- Presence of an amine odour after the addition of KOH treatment.

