## **6.1 Study Objectives**

### **Primary Objectives:**

The objective of this study is to determine whether *L. rhamnosus* GR-1® and *L. reuteri* RC-14® delivered via capsules to the vagina of post-menopausal women over a three day course of treatment can restore and maintain a lactobacilli-dominated microbiota for one week as measured by:

- A decrease in the Nugent Scores from an intermediate score (4 - 6) at baseline to a normal score (0 - 3) following treatment.

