### **Exclusion Criteria:**

1. Use of vaginal lubricants, or any products applied vaginally within three months prior to *Visit 1* and throughout the duration of study participation;
2. A history or currently undergoing immunosuppressive drug therapy, chemotherapy, or radiation therapy;
3. A medical condition which might compromise their immune system functions (such as cancer, leucopenia, HIV-positive, or organ transplant);
4. Antibiotics and/or antifungal medication use within the last four (4) weeks;
5. Oral probiotic supplement use within 3 months prior to *Visit 1* and throughout the duration of the study;
6. Significant changes in diet during the course of the study.
7. Induced menopause due to surgical or medical interventions, such as bilateral oophorectomy, hysterectomy, chemotherapy and radiation treatment;
8. Currently undergoing local or systemic estrogen therapy who are not willing to alter therapy during the course of the study;
9. A Nugent Score of 0 – 3 or greater than 6;
10. History of drug or alcohol abuse;
11. Currently diagnosed with or being treated for a genital infection or urinary tract infection;
12. Individuals with a sexually transmitted disease (self-reported or detected by the Principal Investigator);
13. At enrollment, have any social or medical condition, or psychiatric illness that, in the opinion of the Investigator, would preclude provision of informed consent, make participation in the study unsafe, complicate interpretation of study outcome data, or otherwise interfere with achieving the study objectives;

14. Participation in a clinical trial involving an investigational product within the past three months; subjects who are currently scheduled to participate in another clinical study concurrently; and
15. Known intolerance or allergy to *L. rhamnosus* GR-1® and *L. reuteri* RC-14® or to any product excipient.

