### ***Treatment Phase I - Visit 3 – Day 15 (+/-2 days)***

The following assessments will be performed:

- Subject diaries will be collected and reviewed, and subjects queried regarding any adverse events they may have experienced;
- A vaginal health questionnaire will be completed;
- Five (5) vaginal samples and a vaginal pH measurement will be taken in the same manner as described for Visit 2;
- Randomize subjects with Nugent Scores between four (4) and six (6) as per section 7.2;
- Subjects with a Nugent Score ranging from four (4) to six (6) will be given either six (6) placebo or six (6) probiotic capsules per the randomization and will be instructed to administer them vaginally twice daily, one in the morning and one in the evening, for the next 3 consecutive days. Written instructions for product administration will be provided. Panty liners will be supplied to use on treatment days;
- Subjects will be instructed to keep the capsules in the container and refrigerated between 4°C and 6°C until use;
- Diaries will be dispensed to track compliance and to rate any general vaginal discomfort and record any other adverse events;
- Review concomitant medications; and

- An appointment will be scheduled to return in 4 days (5 days is acceptable) for the Day 19 visit.

*Subjects with a Nugent Score of 7 – 10 at Visit 3 will be treated for Bacterial Vaginosis (BV) as deemed appropriate by the Investigator and discontinued from the study. End of treatment assessments and procedures (Visit 8) should be done.*

*Subjects with a Nugent Score of 0 – 3 at Visit 3 will be asked to return in 7 days (+/-1 day) to have the Nugent Score reassessed. If subjects continue to have a Nugent Score of 0 – 3 after one week, they will be discontinued from the study. End of treatment assessments and procedures (Visit 8) should be done.*

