#### **Treatment Phase II - Visit 6 – Day 36 (+/-2 days)**

The following assessments will be performed:

- Subjects will be queried regarding any adverse events they may have experienced;
- A vaginal health questionnaire will be completed;
- Five (5) vaginal samples and a vaginal pH measurement will be taken in the same manner as described for Visit 2;

- Subjects that have a Nugent Score of 4 – 6 will then be given either six (6) placebo or six (6) probiotic capsules per the randomization and will be instructed to administer them vaginally two (2) times daily for the next 3 consecutive days. Written instructions for product administration will be provided. Panty liners will be supplied to use on treatment days;
- Subjects will be instructed to keep the capsules in the container and refrigerated until use;
- Subjects will be given a diary to track compliance and to rate any general vaginal discomfort and record any other adverse events;
- Review concomitant medications; and
- An appointment will be scheduled to return in 4 days (5 days is acceptable) for Day 40 visit.

*Subjects with a Nugent Score of 7 – 10 at Visit 6 will be treated for BV as appropriate by the Investigator and discontinued from the study. End of treatment assessments and procedures (Visit 8) should be done.*

*Subjects with a Nugent Score of 0 – 3 at Visit 6 will be discontinued from treatment. If these subjects are still colonized with at least one of the probiotic strains they will return for a final study visit on Day 129. All subjects discontinued from treatment will be queried via telephone regarding adverse events on a monthly basis until Day 129.*

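### Section 12 permits withdrawal for a Nugent Score below 3 at no stated visit, which conflicts with the 0–3 rules elsewhere and covers scores that count as treatment success

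*Protocol*

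**What the plan says.** Section 12 introduces its list with "the Investigator may also decide to withdraw a subject from the study in any of the following circumstances apply". The list includes "Subject no longer meets the inclusion or exclusion criteria" and, as a separate item, "Nugent Score less than three (3) or greater than six (6"). Neither item is tied to a visit or phase. The same section tells the Investigator to keep women in the study for as long as can be managed. It also asks that a woman who withdraws has the Visit 8 procedures done promptly.

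Elsewhere the band is 0–3. Section 5.1.3 defines it: "A Nugent Score from 0 to 3 indicates a normal status". Exclusion 9 in section 7.1 bars scores of 0–3 "or greater than 6". The primary objective in section 6.1 counts a fall from 4–6 "to a normal score (0 - 3) following treatment" as success and asks that the restored flora be held for one week. The hypotheses in section 13.1.2.1 use the same bands.

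Two visits in section 8.1 say what to do with a score of 0–3, both before capsules are dispensed. At Visit 3 the woman returns after seven days "to have the Nugent Score reassessed. If subjects continue to have a Nugent Score of" 0–3, she leaves the study. At Visit 6, "Subjects with a Nugent Score of 0 – 3 at Visit 6 will be discontinued from treatment", with follow-up to Day 129 (also in the key to the section 2 schedule). Visits 4, 5, 7 and 8 have no rule for a score of 0–3.

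**The concern.** There are two linked faults. First, the protocol gives different cut-offs and different consequences for the same finding, so two people applying it could treat the same woman differently.

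Second, because section 12 names no visit, its Nugent item also covers the visits after treatment, where a low score is the outcome the trial hopes to see. If an Investigator used it there, follow-up would stop because of the outcome, before the trial could learn whether the effect lasted a week. In a crossover, stopping in the first period also removes the second. A swab that was never taken cannot be recovered by any analysis plan.

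**Working it through.** The protocol states no power or calculated sample size, so there is no figure to reproduce. The check is a comparison of texts, followed by simple arithmetic.

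**Step 1. The rules side by side.**

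| Place | Scores | When | Consequence |
|---|---|---|---|
| Section 12, Nugent item | below 3, or above 6 | no visit named | may be withdrawn from study |
| Section 12, entry-criteria item, read with exclusion 9 | 0–3, or above 6 | no visit named | may be withdrawn from study |
| Section 8.1, Visit 3 | 0–3 | Day 15, before Phase I capsules | retest after 7 days; out of study if still 0–3 |
| Section 8.1, Visit 6, and section 2 key | 0–3 | Day 36, before Phase II capsules | no further treatment; followed to Day 129 |
| Sections 6.1 and 13.1.2.1 | 0–3 | after treatment | primary success |

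**Step 2. Overlap with success.** On the 0–10 scale the Nugent item covers {0, 1, 2, 7, 8, 9, 10}. The success band is {0, 1, 2, 3}. The overlap is {0, 1, 2}, three of the four success scores. The score left out is 3, which the entry-criteria item in the same section does reach.

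**Step 3. What a withdrawal would cost.** Capsules are used on Days 16–18 and 37–39. The first swabs afterwards are at Visit 4 (Day 19) and Visit 7 (Day 40). The one-week swabs are at Visit 5 (Day 26) and Visit 8 (Day 47).

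- *After Visit 4:* the Day 26 value and the whole second period are lost. Doing Visit 8 procedures promptly gives close to a repeat of Day 19, not a one-week value. The Full Analysis Set (section 13.1.1) still admits her on one observation after insertion, but McNemar's test has no pair.
- *After Visit 7:* both periods have been dosed and have a Nugent value. Only the one-week timing of the second is lost.

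**Step 4. How much belongs to section 12.** A woman still at 0–3 on Day 36 loses her second treatment under the Visit 6 rule in any case. Section 12 therefore adds pair loss only for women at 0–2 on Day 19 who would have been back at 4–6 by Day 36. The lost Day 26 value is due to section 12 in every case.

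Assume seven women per sequence and Day 19 scores of 0–2 in 50% on probiotic and 10% to 25% on placebo. The protocol gives none of these figures. The number meeting the Nugent item at Visit 4 is then:

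- 7 × 0.50 + 7 × 0.10 = 4.2
- 7 × 0.50 + 7 × 0.25 = 5.25

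Multiply by the share actually withdrawn to get lost Day 26 values, and again by the share who would have returned to 4–6 to get pairs lost through section 12. With both shares at one half (also assumed), that is 4.2 × 0.25 = 1.05 to 5.25 × 0.25 = 1.31 pairs. The full range runs from 0, if the option is never used, to 5.25.

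**Step 5. Sensitivity of the test.** The protocol does not say which form of McNemar's test is meant; the exact form is assumed here. With d discordant pairs all in one direction, two-sided p = 2 × 0.5^d:

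- d = 5: 0.0625
- d = 6: 0.031

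So at least six are needed. For mixed splits:

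- 8 to 1: 2 × (1 + 9) / 512 = 20/512 = 0.039
- 6 to 1: 2 × (1 + 7) / 128 = 16/128 = 0.125

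Losing two probiotic-only responders would move the result across 5%. The 8-to-1 split is an illustration, not an expected result.

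**The case against.** The best defence is that section 12 only restates the checks made before dispensing. Its wording is permissive, it asks that women be kept in, and the Visit 4 and Visit 7 procedures hand back the diary and book the next appointment with no stopping rule for a normal score. On that reading nobody is told to withdraw a success. This stands as far as it goes: a reader might infer that section 12 requires responders to be withdrawn, and it does not. But the list carries no visit limit, and discretion exercised on the outcome itself is still loss that depends on the outcome.

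A reader might also infer that a score of exactly 3 escapes. It has little practical effect, because the entry-criteria item reaches it, and at Visits 3 and 6 the explicit 0–3 rules govern. What remains is that section 12 disagrees with itself.

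Finally, a reader might blame section 12 for every broken pair. The Visit 6 rule takes the second treatment from women still normal on Day 36 whatever section 12 says, and a withdrawal after Visit 7 breaks no pair.

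**Conclusion.** The inconsistency is certain on the text: the cut-off, the visit and the consequence all differ between section 12 and the other rules. Three of the four success scores are permitted grounds for withdrawal before the one-week swab. The practical size is not certain. It depends on how often an Investigator would use the option and on response rates the protocol does not give.

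It is tempting to say that the comparison would be biased towards no effect. The document does not support that, because the direction depends on how missing periods are handled. If incomplete pairs are dropped, losing probiotic-first responders may hide an effect. If a missing placebo period counts as failure and the probiotic success is kept, the same woman becomes a pair in favour of probiotic, and the bias can run the other way.

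This is an exploratory pilot with 14 women chosen on feasibility, and the rule is optional. The point is a should-fix.

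**What to change.** Reconcile the section 2 key, exclusion 9 in section 7.1, the Visit 3 and Visit 6 rules in section 8.1, and both relevant items in section 12, so that each states the same cut-off, the visit at which it applies and what follows. Changing only the number in the Nugent item would not be enough, because the entry-criteria item reaches the same women.

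Add a sentence that the Nugent Scores at Visits 4, 5, 7 and 8 are outcome measurements and that their scheduled collection continues when a score is in the normal range. This concerns data collection only. Which threshold or treatment rule applies is for the sponsor to decide.

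The cost is a short protocol amendment, with no new visits or samples.

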## **13 STATISTICS**

### **13.1 Statistical Methods**

A complete statistical analysis plan will be finalized prior to the enrolment of the first subject into the study. All analyses and summaries, in table and graph form, will be presented by treatment group, unless specified otherwise.

Frequency distributions (n, proportions) will be used to present categorical data such as Nugent Scores and symptoms. Descriptive statistics such as n, mean, minimum, maximum, median and standard deviation (SD) will be used to present continuous variables such as age. No statistical sample size testing was performed.

#### **13.1.1 Analysis Populations**

**Safety Set:** All randomized subjects who received the INHP at any dose or placebo, will be included in the safety analyses.

**Full Analysis Set:** All randomized subjects will be analyzed following the principle of intention-to-treat (ITT) provided they received the INHP or placebo and had at least one efficacy observation after first insertion.

**Per protocol Set:** All subjects who are compliant with the study protocol (i.e., who do not experience any major protocol deviations), who received the INHP or placebo and had at least one efficacy observation after first insertion.

The primary efficacy analysis will be based on the Full Analysis Set, although a secondary analysis will also be performed based upon the Per-Protocol Set (if there are differences) to assess the sensitivity of the analysis to the choice of analysis population.

The analyses of all other efficacy endpoints will be based upon the Full Analysis Set only. All safety analyses will be based upon the Safety Set.

#### **13.1.2 Efficacy Analysis**

Efficacy endpoints shall include the Nugent Scores and symptoms of itching, irritation, and general vaginal discomfort, as well as other symptoms.

##### **13.1.2.1 Nugent Score Analysis**

$$H_0: \pi_A = \pi_P$$

$$H_a: \pi_A \neq \pi_P$$

$\pi_A$  denotes proportion of subjects used intravaginal probiotic capsules had shown improvement in Nugent Score from intermediate (4-6) to normal status (0-3)

$\pi_P$  denotes proportion of subjects used intravaginal placebo capsules had shown improvement in Nugent Score from intermediate (4-6) to normal status (0-3)

McNemar's test will be utilized to test the hypothesis at 5% level of significance, 2-sided.

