#### 13.1.3.1 Additional Nugent Score Analyses

Change in Nugent Score from baseline (no treatment phase) through the treatment phases and follow-up will be summarized and compared between the test articles.

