### **13.1.4 Safety Analysis**

Safety analysis will be completed utilizing the data in the Safety Set as defined in Section 13.1.1. Adverse events occurring during the study and follow-up will be tabulated by Body System, severity, and Investigator reported relationship to the INHP. Any deaths or serious INHP associated AE cases will be summarized.

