## **13.2 Sample Size and Power Considerations**

No formal sample size calculation was performed for this study. The number of subjects to be randomized is based on feasibility and practical considerations for such an exploratory study. It is planned that a total of fourteen (14) subjects will be randomized in this study.

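### Progression to Nugent 7-10 is not a defined outcome, and discontinuing the women who reach it leaves the later change-in-score summaries to those who had not yet worsened

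*Protocol*

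**What the plan says.** **Natural course.** Section 5.1.3: "Women with an intermediate Score have an approximately equal probability of developing either BV or a normal microbiota". It gives no rate and no time frame. Section 5.3.2.2 names prevention of infections such as BV as part of the product's intended use.

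**Primary analysis.** Section 13.1.2.1 tests equality of two proportions. The first is the "proportion of subjects used intravaginal probiotic capsules had shown improvement in Nugent Score from intermediate (4-6) to normal status (0-3"; the second is the same for placebo. "McNemar's test will be utilized to test the hypothesis at 5% level of significance, 2-sided".

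**Discontinuation.** Section 10.3: "In the event of a Nugent Score greater than or equal to seven (7), the subject will be discontinued from the study", with an antibiotic prescribed. Section 10.1 says the same for a 7-10 score at any time. Sections 8.1 (Visits 3 and 6) and 12 call for the Visit 8 procedures when a woman leaves.

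**Other Nugent displays.** Section 13.1.3.1: "Change in Nugent Score from baseline (no treatment phase) through the treatment phases and follow-up will be summarized and compared between the test articles". Section 13.1 adds frequency distributions of Nugent Scores, with summaries by treatment group.

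**Safety.** Section 13.1.4: "Adverse events occurring during the study and follow-up will be tabulated by Body System, severity, and Investigator reported relationship to the INHP". Section 11.1 defines an adverse event broadly. Neither section names a 7-10 smear or BV rescue.

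**Timing.** Nugent swabs are taken at Visits 1 to 8. The first visit after each three-day course is Day 19 or Day 40, and the one-week visit is Day 26 or Day 47. The primary objective (6.1) asks whether a normal microbiota is kept for one week.

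**The concern.** From an intermediate score a woman can move two ways. The protocol defines an outcome for one direction and a discontinuation rule for the other, but no outcome for that other direction. Three things follow.

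- The primary endpoint cannot separate a woman who goes from 5 to 8 and is rescued from one who stays at 5.
- No table accumulates, over a period, how many women on each product reached 7-10 or needed a BV antibiotic.
- The score itself decides who remains for the next visit. A later summary of change is then conditional on not having worsened, and the condition may remove more women from one product than from the other.

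The adverse event tables do not reliably fill the gap. Section 5.1 says that about half of women with BV report no signs or symptoms, so BV found only on a smear might never be entered as an event. For a product meant to keep women out of BV, the report could show falling scores at one week without a plain count of those who went the other way.

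**Working it through.** The protocol states no power or expected rate ("No formal sample size calculation was performed for this study"), so there is no figure to reproduce. The checks below trace the rules and then use assumed rates.

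**1. A woman who scores 8 on Day 19**

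- Primary endpoint: not improved, the same as a score of 5.
- Day 19 change in score and frequency table: her 8 is shown under the product she received.
- Day 26: no scheduled score, because she has been discontinued.
- Phase II: no outcome on the other product.
- Adverse event table: she appears only if someone records BV as an event.
- Exit sample: section 12 asks for Visit 8 procedures on withdrawal. The protocol does not say whether this sample precedes the antibiotic or to which visit it is assigned.

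**2. Primary endpoint under assumed rates**

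Placebo 40% normal, 10% BV; probiotic 40% normal, 40% BV: the comparison is 40% against 40%. With probiotic at 50% normal and 40% BV it is 50% against 40% in the probiotic's favour, with four times the BV.

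**3. Score summary after exits**

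Assumed: all start at 5; normal = 2, intermediate = 5, BV = 8; every BV case is found at the first post-dose visit; other scores then stay put. With proportions N, I and B:

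- all women: 2N + 5I + 8B
- women remaining: (2N + 5I) / (1 − B)

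| Product, N/I/B | All women | Remaining |
|---|---|---|
| Placebo 0.4/0.5/0.1 | 0.8 + 2.5 + 0.8 = 4.1 | 3.3/0.9 = 3.67 |
| Probiotic 0.4/0.2/0.4 | 0.8 + 1.0 + 3.2 = 5.0 | 1.8/0.6 = 3.0 |
| Probiotic 0.4/0.3/0.3 | 0.8 + 1.5 + 2.4 = 4.7 | 2.3/0.7 = 3.29 |
| Probiotic 0.4/0.4/0.2 | 0.8 + 2.0 + 1.6 = 4.4 | 2.8/0.8 = 3.5 |

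In each probiotic row the all-women mean is worse than placebo and the remaining-women mean is better. In the 40% BV row the change from 5 is 0.0 against −0.9 in all women, and −2.0 against −1.33 in those remaining.

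**4. Sensitivity to timing and direction**

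If only half of the BV cases are found at the first visit (assumed) and the rest at the one-week visit, the later are counted there. Probiotic at 40% BV: (0.8 + 1.0 + 0.2×8)/0.8 = 4.25. Placebo: (0.8 + 2.5 + 0.05×8)/0.95 = 3.89. The ranking is then correct, but the gap shrinks from 0.9 to 0.36. If the labels are swapped, so that placebo has more BV, the same arithmetic works against the probiotic.

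**5. What the sample can support**

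"It is planned that a total of fourteen (14) subjects will be randomized in this study". An exact two-sided McNemar test needs six discordant pairs, all one way: 2×0.5^6 = 0.031, against 2×0.5^5 = 0.0625 for five. With BV at 40% against 10%, independent within a woman, the discordant probabilities are 0.4×0.9 = 0.36 and 0.1×0.6 = 0.06, and exact power with 14 complete pairs is about 22%. Pairs would also be lost: with an assumed equal split of 7 per sequence and BV in 10% to 40% after Phase I, 0.7 to 2.8 of the 7 have no Phase II outcome.

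**The case against.** The strongest reply is that the harm is visible. A reader might infer that BV is never compared between the products. The protocol does not support that: section 13.1.3.1 compares change in score between the test articles, section 13.1 tabulates Nugent Scores by treatment group, and a 7-10 score enters both at the visit where it is found. Read next to the Day 26 or Day 47 summary, the Day 19 or Day 40 summary would show the worsening and the fall in numbers. A 7-10 score first seen on Day 26 or Day 47 is not lost from its period.

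Nor is the safety route closed. New BV needing an antibiotic plausibly meets the definition in section 11.1, reasons for withdrawal must be described, and concomitant medications are reviewed at each visit. Section 13.1.1 keeps dosed women with a post-insertion observation in the Full Analysis Set. Handling of exit samples and missed visits may properly be left to the SAP. Scoring BV as non-response is ordinary for a responder endpoint and matches the objective in 6.1.

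All of this stands, and it limits the point. It does not supply a defined outcome or a count per product and period, and it does not change the fact that later visits exclude women because of the variable being summarised.

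**Conclusion.** The point holds as a gap in outcome definition and reporting. Progression to 7-10 is measured and triggers discontinuation, but it is merged with no change in the primary test, shown only visit by visit elsewhere, and followed by score summaries of women who had not yet worsened.

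The size is not known. The reversals in the table rest on assumed rates, on scores of 2, 5 and 8, and on every BV case being found at the first post-dose visit; with half found later the difference is only diluted. Section 5.1.3 gives relative likelihood, not a rate over ten days.

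A reader might infer that the plan is biased towards the probiotic. The protocol does not support that either. The distortion favours whichever product has more early BV, and women at 0-3 at Visit 6 also receive no Phase II capsules, which removes pairs in which Phase I succeeded. The primary endpoint itself need not change. This is a cheap, worthwhile improvement, and with 14 women its output is descriptive only.

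**What to change.** **Section 13.1.4.** Report, by product and period, the number and proportion of women with any Nugent Score of 7-10 or BV antibiotic rescue after the first capsule of that period. The denominator is the women who received that product in that period. Add exact confidence intervals and a by-woman listing, and state that the table is descriptive.

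**Section 13.1.3.1.** Summarise each visit as normal / intermediate / BV, and keep a woman who reached 7-10 in the BV category at the later scheduled visits of that period. Do not use scores taken after the antibiotic, including those from exit Visit 8 samples.

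**Cost.** Two sentences and one extra table from scores already collected. The score summary may look less favourable for a product with more BV. Treatment, rescue and discontinuation rules are untouched.
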